### Analysis of other secondary outcomes

The rate of IRIS and the rate of relapse (defined as antifungal treatment intensification or re-treatment) will be modeled with cause-specific proportional hazards models with treatment as the only covariate and stratification by HIV infection status.

The visual acuity at 10 weeks is recorded on a 6 point scale and will be summarized by treatment arm for each eye separately, and overall where “overall” is defined as the worst recorded acuity of either eye. The odds of having “normal acuity” (amongst all surviving patients with a visual assessment) will be informally compared between the treatment arms with a logistic regression model adjusted for HIV status.

The time to the first new neurological event or death until 10 weeks will be analyzed in the same way as overall survival. Longitudinal measurements of intracranial pressure during the first 2 weeks will be modeled using a mixed effect model as described for the primary outcome. CD4 cell count at baseline and 10 weeks will be summarized and the change compared between the two groups based on a linear regression model with treatment as the main covariate and adjustment for HIV status and baseline CD4 cell count.

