## Background

Worldwide cryptococcal meningitis results in approximately 625 000 deaths each year, most occurring within 3 months of diagnosis
^1^. It is the leading cause of death in HIV patients in Asia and Africa affecting 3.2% of the HIV infected population per year
^1^. Despite improvements in access to HIV care, the WHO estimates that even if 80% access to HIV treatment is achieved, there will be 6.5 million AIDS deaths p.a. by 2030
^2^. Thus, CM is likely to remain a significant health burden for the foreseeable future. While cryptococcal meningitis predominantly occurs in HIV infected patients, patients with other forms of immunosuppression are also affected
^3,
4^. Furthermore, in Viet Nam we see disease in apparently immunocompetent patients (N = 30 each year at the Hospital for Tropical Diseases and Cho Ray Hospital) due to infection with
*Cryptococcus neoformans* var.
*grubii*, or, more rarely,
*C. gattii*
^5^.

There has been no major advance in the treatment of cryptococcal meningitis since the 1980’s, and the 90 day case fatality rate of cryptococcal meningitis remains unacceptably high, estimated at 55% in Asia and 70% in Africa
^1^. The mainstays of induction therapy are drugs that are over 50 years old – amphotericin B and flucytosine - although these are often poorly available where disease burden is highest
^6,
7^. While amphotericin monotherapy is undoubtedly superior to fluconazole monotherapy, amphotericin combination therapy has only recently been shown to reduce mortality when compared with amphotericin monotherapy in a randomized controlled trial in Vietnam
^8^. In this study, in Vietnamese patients receiving gold standard treatment with amphotericin and flucytosine, the death rate at 10 weeks and 6 months was 31% and 35%. This compared with 33% and 46% in patients receiving amphotericin-fluconazole induction therapy (the current WHO guideline), and was significantly better than in patients receiving prolonged amphotericin monotherapy, where the death rates were 44% and 54% respectively
^8^. A biological explanation for these better outcomes is that the amphotericin-flucytosine combination has increased sterilising power – it results in significantly more rapid clearance of yeast from cerebrospinal fluid than amphotericin monotherapy

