### Secondary endpoints

***Survival until 10 weeks after randomization.*** International treatment guidelines recommend 10 weeks of high dose antifungal therapy for cryptococcal meningitis – an initial phase of amphotericin based induction therapy for 2 weeks followed by 8 weeks of moderate to high dose fluconazole. The rate of survival until this 10 week period of therapy is completed is a frequent endpoint in trials of treatment for cryptococcal meningitis
^8,
9,
44^. Improvements in EFA over the first 2 weeks of treatment have been associated with improved survival at 10 weeks. Therefore survival until 10 weeks after randomization will be a secondary endpoint in this study.

***Disability at 10 weeks.*** Disability is an expected consequence of cryptococcal meningitis, including blindness, deafness and other focal neurological deficits. In addition to improving the sterilizing power of antifungal therapy, Tamoxifen may also reduce the rates of disability in survivors. Neurological disability will be assessed using the modified Rankin score and the Two Simple Questions and classified as good, intermediate, severe disability, or death, as previously described
^45^.

***Adverse events.*** The proportion of patients with any grade 3 or 4 adverse event, serious adverse event, or unexpected serious adverse event will be compared between treatment groups.

***Rate of IRIS until 10 weeks (in HIV infected patients only).*** We will model the rate of IRIS over time with a cause-specific hazards model taking into account the competing risk of prior death. CM-related IRIS will be defined as per the recent proposed definition
^46^.

***Rate of Cryptococcal meningitis relapse.*** A pragmatic definition of relapse will be used. This is defined as either intensification of antifungal therapy above that according to the study antifungal schedule, or readmission for treatment of cryptococcal disease.

***QT prolongation.*** Prolongation of the QT interval is a potential side-effect of both Tamoxifen and fluconazole, although it is not clear that either drug increases the risk of Torsade de Pointes, a potentially life-threatening arrhythmia. The QT interval will be estimated manually from 3 chest and 3 limb leads from a high resolution (50mm/sec) 12-lead ECG. The median value will be determined and used to calculate the corrected QT interval (QTc) using Framinghams’ formula.

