***Visual deficit at 10 weeks.*** Visual deficit occurs in 5–40% of patients with cryptococcal meningitis depending upon underlying immune status
^5,
8^. The pathogenesis is unclear. We will compare the incidence of blindness and other visual deficit between treatment groups. Visual deficit will be assessed using a simple 6 point scale, as used in previous studies (see
Table 3).

***Time to new neurological event or death until 10 weeks.*** A neurological event is defined as a fall in Glasgow coma score by ≥2 points for ≥2 days from the highest previously recorded Glasgow coma score (including baseline) or the occurrence of any of the following adverse events: cerebellar symptoms, coma, hemiplegia, paraplegia, seizures, cerebral herniation, new onset blindness or deafness, or cranial nerve palsy.

***Longitudinal measurements of intracranial pressure during the first 2 weeks.*** Intracranial pressure (ICP) will be measured at study entry, day 3, 7, and 14, and if clinically indicated (depending on local practice). The main outcomes are longitudinal ICP-measurements until day 14.

Clinical need and local practice will determine the frequency of lumbar punctures post day 14 and clinician’s diagnoses of raised ICP based upon the presence of headache, nausea, diurnal and postural variation, relief with lumbar puncture and presence of papilloedema. Thus, these measures will only be descriptively analyzed.

***CD4 count at 10 weeks.*** CD4 count measurement is indicated in HIV infected patients, and CD4 lymphopenia has been described in HIV uninfected patients with cryptococcal meningitis. Moreover, Tamoxifen may reduce CD4 cell apoptosis which may be beneficial
^47^.

***Blood and CSF concentrations of amphotericin, Tamoxifen and fluconazole.*** Pharmacological data on antifungal drugs are lacking. Dosing has been inferred from studies in healthy volunteers, or patients with other diseases. There are no studies of combination therapy at the doses currently recommended
^48–

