### Randomization

Randomization will be 1:1 to either Tamoxifen augmented or standard antifungal therapy. Block randomization with stratification by hospital of enrolment and by HIV infection status, and variable block sizes of 4 and 6, respectively, will be used to assign subjects to treatment. The randomization list will be generated according to OUCRU standard operating procedures. In brief, the Research Biostatistician will set up statistical code to generate the randomization list and transfer it to the central Study Pharmacist. The Study Pharmacist will change the random seed, i.e. the initialization of the random numbers generator, in the statistical code in order to blind the Research Biostatistician and then run the code to prepare the final randomization list for treatment preparation. The randomization list will be password protected and stored on a secure server to which only the Study Pharmacist has access.

Based on the randomization list, the central Study Pharmacist will generate identical sealed treatment packs for each study ID and distribute them to the sites in batches as required. All treatment packs will be identical in appearance and will contain either Tamoxifen and fluconazole or fluconazole alone. Each pack will contain sufficient fluconazole for the first 2 weeks of treatment. Enrolment logs specific to each ward will be used to assign patients to the next available sequential number and corresponding sealed treatment pack.

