### Disability at 10 weeks.

The disability score at week 10 follow-up is defined as the higher (worse) of “ the two simple questions” and the Rankin score assessed at that time point, and will be categorized as good outcome, intermediate disability, severe disability, or death (in case the patient died before 10 weeks) as previously described
^45^. The ordinal 10-week score (“good”>”intermediate”>”severe”>”death”) will be compared between the two arms with a proportional odds logistic regression model depending on the treatment arm and HIV infection status. The result will be summarized as a cumulative odds ratio with corresponding 95% confidence interval and p‐value. Patients lost to follow up will be analyzed according to their last recorded disability status. If the rate of patients lost to follow-up exceeds 10%, we will also perform an alternative analysis based on multiple imputation of missing values.

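### The visual endpoint is described as incidence of deficit, but the only between-arm model is normal acuity among assessed week-10 survivors, which can be biased if treatment changes survival

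*Protocol article*

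**What the plan says.** All references are to the protocol article. Under Secondary endpoints, Visual deficit at 10 weeks, the stated aim is: "We will compare the incidence of blindness and other visual deficit between treatment groups". The same paragraph gives a background rate: "Visual deficit occurs in 5–40% of patients with cryptococcal meningitis depending upon underlying immune status". Clinical monitoring lists visual deficit for week 10.

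Under Analysis of other secondary outcomes, the 6-point score is summarised by arm for each eye and for the worse eye. The one between-arm comparison takes normal acuity as its outcome and is specified as follows: "amongst all surviving patients with a visual assessment) will be informally compared between the treatment arms with a logistic regression model adjusted for HIV status".

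Other sections treat death differently:
- Analysis populations makes all randomised patients with cryptococcal meningitis the primary population for every analysis.
- The disability score has a worst category of "death (in case the patient died before 10 weeks".
- The IRIS endpoint is to be modelled with prior death as a competing risk.
- The neurological-event endpoint is combined with death and names new-onset blindness as a component.

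**The concern.** Incidence over follow-up and acuity in week-10 survivors are different quantities. A patient who goes blind on day 20 and dies on day 45 is an incident case that the model never sees. A patient with blurred vision at entry and unchanged vision at week 10 is not an incident case but is modelled as not normal.

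The survivor restriction matters most. Survival to week 10 is observed after randomisation, and the protocol expects better yeast clearance to improve it: "Improvements in EFA over the first 2 weeks of treatment have been associated with improved survival at 10 weeks". If survival differs, the two groups of survivors are no longer comparable by virtue of randomisation. Suppose the extra tamoxifen survivors are sicker patients with more visual damage. The odds of normal acuity would then be lower on tamoxifen even if the drug did nothing to vision. The trial is meant to inform the decision on a larger study, so a spurious signal of visual harm would be unhelpful.

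**Working it through.** The protocol gives no expected figure for this comparison, so there is none to reproduce. The check asks how far the survivor odds ratio moves from 1 when treatment has no effect on vision.

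**Inputs from the protocol article**
- 25 patients per arm (Study design; Sample size).
- Control 10-week mortality pC = 0.33. Background, after giving the amphotericin–flucytosine figures: "This compared with 33% and 46% in patients receiving amphotericin-fluconazole induction therapy".
- Comparator 10-week mortality of 0.31 on amphotericin–flucytosine (Background). The first power simulation assumes tamoxifen has a similar effect on clearance to that regimen, so 0.31 is the nearest analogue for tamoxifen mortality pT. The protocol states no tamoxifen mortality.

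**Assumptions not in the protocol**
- Larger mortality differences: pT = 0.20 to 0.25.
- Deficit risk a = 0.05 to 0.10 in patients who would survive in either arm.
- Deficit risk b = 0.30 to 0.40 in patients who die on control but survive on tamoxifen.
- Nobody dies on tamoxifen who would have survived on control. HIV adjustment is ignored.

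**Formulas**
- Deficit in control survivors = a.
- Deficit in tamoxifen survivors: dT = [(1 − pC)·a + (pC − pT)·b] / (1 − pT).
- Odds ratio of normal acuity, tamoxifen to control: OR = [(1 − dT)/dT] / [(1 − a)/a].

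**Patients leaving the denominator.** 25 × 0.33 = 8.25 controls, which leaves 16.75.

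**Protocol's own analogue, pT = 0.31, a = 0.10, b = 0.40**
- dT = (0.67 × 0.10 + 0.02 × 0.40) / 0.69 = 0.075 / 0.69 = 0.109.
- OR = 8.20 / 9.00 = 0.91.
- Expected deficits: 17.25 × 0.109 = 1.9 on tamoxifen and 16.75 × 0.10 = 1.7 on control.
- Across the ranges of a and b, OR runs from 0.82 (a = 0.05, b = 0.40) to 0.94 (a = 0.10, b = 0.30).

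**Larger assumed difference, pT = 0.20, a = 0.10, b = 0.40**
- dT = (0.067 + 0.13 × 0.40) / 0.80 = 0.119 / 0.80 = 0.149.
- OR = 5.72 / 9.00 = 0.64.

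**Extremes for pT = 0.20 to 0.25**
- pT = 0.20, a = 0.05, b = 0.40: dT = 0.0855 / 0.80 = 0.107, OR = 0.44.
- pT = 0.25, a = 0.10, b = 0.30: dT = 0.091 / 0.75 = 0.121, OR = 0.80.

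**Where the bias vanishes.** If pT = pC, or if a = b, then dT = a and OR = 1.00.

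**What an all-randomised composite shows.** Alive with normal acuity, at pT = 0.20, a = 0.10, b = 0.40, is 0.67 × 0.90 = 60.3% on control and 0.80 × 0.851 = 68.1% on tamoxifen. Vision is unaffected by construction, so this whole difference is mortality.

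**The case against.** The case for leaving the plan alone has several parts.

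The endpoint's heading, Clinical monitoring and the analysis section all refer to week 10, so the endpoint can be read as status at that visit with incidence as a loose word. That reading is fair and softens the mismatch. It does not remove the selection on survival.

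The restriction is stated openly, the comparison is called informal, and the full scale is also tabulated by arm. All true, and this keeps severity low.

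Blindness before death is not lost to the trial. It is a component of time to new neurological event or death, and a grade 3 or 4 event would appear in the adverse event comparison. This stands in part. The composite counts only the first event, and its named visual component is blindness, not lesser deficits.

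The inputs that drive a large bias are not the protocol's. Its 5–40% range is by immune status, not by whether a patient would have died, and HIV status is already a covariate in the visual model. This stands in full, and so the larger odds ratios are conditional illustrations only.

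A reader might go further and infer that the planned analysis would reverse the treatment comparison. The documents do not support that. The calculation assumes no visual effect, so there is nothing to reverse. A reversal needs an added assumption of true visual benefit as well as unequal mortality and higher deficit risk in those who would die. The protocol gives neither tamoxifen mortality nor deficit risk by survival, and no effect on vision.

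**Conclusion.** The point holds in a limited form. The protocol states one quantity, incidence, and models another, normal acuity in assessed survivors, without saying that the second is conditional on an outcome treatment may affect. The resulting odds ratio is biased if mortality differs between arms and visual loss is commoner in patients who would otherwise have died. With the protocol's own mortality analogue and the assumed 10% versus 40% split, the bias is small, about 0.91. It is 0.44 to 0.80 only if tamoxifen mortality is assumed to be 20–25%, and nil with equal mortality. If tamoxifen raised mortality, the direction would be the opposite. Severity is low, because this is an informal comparison of a secondary endpoint. It is still worth correcting: the repair is cheap and the protocol already uses better handling of death for disability and IRIS.

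**What to change.** 1. Keep the survivor model, but describe it as conditional on survival to week 10 and on having a visual assessment, and do not call it incidence. Beside it, report by arm the number of deaths and of survivors without an assessment.
2. Add one comparison in all randomised patients, adjusted for HIV status. Use either the worse-eye score with death as the worst category in a proportional odds model, as is done for disability, or alive with normal acuity as a yes/no outcome. State that it combines death and vision, and state how survivors without an assessment are handled.
3. For incidence, analyse new-onset blindness from the recorded neurological events in all randomised patients, with death as a competing event, as already planned for IRIS.

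No new baseline vision score is proposed: Trial status says enrolment has finished. Pre-existing deficit can be separated only if vision at entry was recorded.

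The cost is wording and two supplementary analyses from data already planned; Trial status says analysis is still under way. The drawback is that the all-randomised figure can show a benefit that is entirely mortality, as the working does, so it supplements the survivor result and does not replace it.

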## Analysis populations

The primary analysis population for all analysis is the full analysis population containing all randomized patients except for those mistakenly randomized without cryptococcal meningitis. Patients will be analyzed according to their randomized arm (intention-to-treat). In addition the primary endpoint will be analyzed on the per-protocol population which will exclude the following patients: major protocol violations and those receiving less than 1 week of administration of the randomized study drug for reasons other than death.

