## Study procedures

### Recruitment

The target population for study screening is any patient known or suspected to have cryptococcal meningitis. To enter the study patients must be confirmed to have cryptococcal meningitis according to the definition in the inclusion criteria. According to the clinical care of the treating hospital, patients suspected of having cryptococcal meningitis will undergo:

a) an IMMY lateral flow cryptococcal antigen test (LFA) on serum, whole blood, plasma, or urine

AND/OR

b) blood culture for
*Cryptococcus*

AND/OR

 c) a lumbar puncture with an lateral flow cryptococcal antigen test (Ref CR2003, IMMY, OK, USA), and/or microscopic examination of CSF, and/or culture of CSF. 

When the results of the IMMY lateral flow test (plasma, serum, urine or CSF), or CSF microscopy, or blood or CSF culture are available study staff may approach the patient regarding the study. Only patients 18 years or older who are not known to be pregnant and who have evidence of cryptococcal disease from one of the specified tests will be approached. 

A study staff member will invite the patient to discuss the details of the study. If the patient is judged by the staff to be unfit or unable to give informed consent, an acceptable representative will act on their behalf for the following procedures. The study staff will give the patient/representative a copy of the informed consent form and explain the details of the study including the study procedures, risks and benefits, financial and confidentiality considerations, treatment alternatives and how to obtain more information. The study staff will invite the patient/representative to ask questions and will endeavour to ensure that s/he understands the information given. The study staff will then ask the patient/representative to consider study participation. Those who refuse consent will be treated as per the best available standard care and will not have any study related procedures performed. 

Those who consent to the study will sign and date two copies of the informed consent form. The study staff will also sign and date the two copies. 

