## Adverse events

### Definition of adverse events

An adverse event (AE) is any undesirable event that occurs to a study participant during the course of the study whether or not that event is considered related to the study drug. An AE can, therefore, be any unfavorable and unintended sign (including an abnormal laboratory finding, for example), symptom, or disease temporally associated with the study drug, whether or not considered related to the study drug.

Examples include:

An increase in severity (grade) or frequency of a pre-existing abnormality or disorder (events that are marked by a change from the participant’s baseline/entry status, including changes in blood tests such as electrolytes)All reactions from sensitivity or toxicity to study drugInjuries or accidents (e.g., for a fall secondary to dizziness, “dizziness” is the event and the injury secondary to the fall is the “outcome”)New clinically significant abnormalities in clinical laboratory values, physiological testing or physical examination.

Stable chronic conditions, such as arthritis, which are present prior to clinical trial entry and
do not worsen are not considered AEs and will be documented in the subject’s clinical chart as medical history. 

Clinical or laboratory events are considered adverse events only if they occur after the first dose of study treatment and before the patient completes trial participation. (See below for reporting of adverse events.)

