## Analysis of the primary endpoint: early fungicidal activity (EFA)

All recorded longitudinal quantitative fungal count measurements up to day 17 (allowing for some delays in the day 14 measurements) will be included in the analysis. EFA will be modeled based on a linear mixed effects model with longtitudinal log
_10_-CSF quantitative culture fungal counts as the outcome, interaction terms between the treatment groups and the time since enrolment of the measurement as fixed covariates and random patient-specific intercepts and slopes. The lowest measurable quantitative count is 5 CFU/ml and values below the detection limit (which correspond to recorded values of 0) will be treated as <4.5 CFU/ml, i.e. non-detectable measurements will be treated as left-censored longitudinal observations in the analysis as we have done previously
^8^.

Based on this model, EFA will be compared between the two treatment arms in all patients (intention to treat), in the per-protocol population, and subgroups defined by HIV status (uninfected; infected) and baseline fungal burden (<5 log
_10_ CFU/ml; ≥5 log
_10_ CFU/ml).

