### Adverse events.

The frequency of serious and grade 3 & 4 adverse reactions as well as the frequency of specific adverse events will be summarized (both in terms of the total number of events as well as the number of patients with at least one event). The proportion of patients with at least one such event (overall and for each specific event separately) will be summarized and (informally) compared between the two treatment groups based on Fisher’s exact test.

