### QT prolongation

The QTc will be classified as “normal” (<450ms for males, <460ms for females), mildly prolonged (≥450ms for males or ≥460 for females but ≤500ms) and prolonged (>500ms). The frequency of patients with a maximum QTc in these categories will be summarized for the following time intervals: day 1 (baseline), days 2-3, 4-7, 8-14, and after day 14. Comparisons will be with a proportional odds logistic regression model depending on the treatment arm and HIV infection status.

The maximum absolute change from baseline of the QTc during follow-up will also be summarized; the comparison between treatment groups will be based on a linear regression model with treatment as the main covariate and adjustment for HIV status and the baseline QTc interval.

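### One analysis population serves every analysis, so a dosed patient found not to have cryptococcal meningitis is left out of the adverse-event and QTc comparisons

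*Protocol article*

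**What the plan says.** *Analysis populations* sets a single population: "The primary analysis population for all analysis is the full analysis population containing all randomized patients except for those mistakenly randomized without cryptococcal meningitis". Patients are then analysed in the arm to which they were randomised. The only other set is a per-protocol population, and it is added for the primary endpoint alone.

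The safety paragraphs describe their summaries without naming a population. Under *Adverse events* in the analysis section: "The proportion of patients with at least one such event (overall and for each specific event separately) will be summarized". Under *QT prolongation*: "The frequency of patients with a maximum QTc in these categories will be summarized for the following time intervals". The article nowhere mentions a set defined by exposure.

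Two other statements bear on the point. *Definition of adverse events* ties events to dosing: "Clinical or laboratory events are considered adverse events only if they occur after the first dose of study treatment". *Recruitment* limits who can enter: "To enter the study patients must be confirmed to have cryptococcal meningitis according to the definition in the inclusion criteria".

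For the primary endpoint, the analysis section uses a shorter label: "EFA will be compared between the two treatment arms in all patients (intention to treat), in the per-protocol population".

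**The concern.** The exclusion depends on diagnosis. That can be defended for clearance of yeast from CSF, because a patient without the infection has nothing to clear. It has no such justification for safety. A patient given tamoxifen and fluconazole is informative about QTc and other toxicity whatever the final diagnosis turns out to be. The protocol therefore defines adverse events by exposure but filters the patients who are counted by diagnosis.

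Safety matters more here than in many phase II trials. Showing that tamoxifen can be given safely with amphotericin and fluconazole is a listed secondary aim. The abstract singles out QT prolongation as a side effect of particular interest. The *Prolonged QTc* section expects roughly 10–50% of patients to develop a prolonged interval on treatment. The results are meant to inform the decision on a larger trial, and with 25 patients per arm a single missing patient shows in the tables.

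**Working it through.** The protocol gives no figure for this point, so there is none to reproduce. The check has two parts.

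**1. Does the exclusion reach the safety analyses?**

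- *Analysis populations* covers every analysis and removes one class of patient.
- *Adverse events* and *QT prolongation* (analysis paragraphs) give no population of their own, so the general rule applies.
- The per-protocol set is only an addition for the primary endpoint and does not change this.
- *Definition of adverse events* starts the clock at the first dose, so a dosed patient without the disease can have a recorded adverse event and still be outside the analysed set.

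The exclusion therefore does reach them. This follows from a rule the protocol states, not from detail it leaves out.

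**2. How much can one patient move a result?**

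Input: 25 patients per arm (*Study design*; *Sample size and power considerations*). The event counts and risks below are assumptions for illustration.

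Suppose x of 25 patients in an arm have the event, and one of those x is excluded. The fall in the rate is

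x/25 − (x − 1)/24 = (25 − x)/600.

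- x = 1: 24/600 = 4.0 points, from 1/25 (4.0%) to 0/24 (0%).
- x = 6: 19/600 = 3.2 points, from 6/25 (24.0%) to 5/24 (20.8%).

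If the excluded patient had no event, the rate rises by x/24 − x/25 = x/600, which is 1.0 point at x = 6. The direction is not fixed.

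The chance of seeing at least one event in an arm is 1 − (1 − p)^n:

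| True risk p (assumed) | n = 25 | n = 24 | n = 23 |
|---|---|---|---|
| 2% | 39.7% | 38.4% | 37.2% |
| 5% | 72.3% | 70.8% | 69.3% |
| 10% | 92.8% | 92.0% | 91.1% |

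For a between-arm comparison, take 6/25 on tamoxifen and 0/25 on control, using Fisher's exact test (the protocol's test for adverse events):

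- nobody excluded: 24.0% v 0%, p = 0.022;
- one patient with the event excluded: 20.8% v 0%, p = 0.022;
- two patients with the event excluded: 4/23 = 17.4% v 0%, p = 0.046.

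One exclusion moves the reported rate but, in this example, not the p-value. It takes two excluded patients, both with the event, to move the p-value noticeably.

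**The case against.** The best defence is that the case will hardly ever arise and that harm would not go unseen if it did. The diagnosis has to be confirmed before entry, and *Screening* allows randomisation only once all criteria have been verified. Grade 3 and 4 events and all arrhythmias are recorded. Serious events go to the Principal Investigator within 3 days and to the local IRBs monthly. Cardiac and unexpected serious events reach the DSMB within 10 days, and the DSMB also makes an unblinded safety review after the first 20 patients. None of this is limited to the full analysis population. Calling that population primary also leaves room for a supplementary table.

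This defence stands on patient protection and on rarity. It does not put an excluded patient back into the final comparison by arm, which readers will use to judge safety. A separate analysis plan might define a safety set, but that would depart from a protocol sentence that covers all analyses.

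A reader might infer three stronger points, and the article does not support them:

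- **That all wrongly randomised patients are removed.** Only those without cryptococcal meningitis are. Someone randomised in breach of another criterion, such as the baseline QTc limit, stays in.
- **That the primary-endpoint section contradicts the population definition.** *Analysis populations* defines the set, and the primary-endpoint section names it loosely to separate it from the per-protocol set. The label needs tidying, but the two passages can be read together.
- **That efficacy exclusions will be judged after randomisation with arm and outcome known, and so bias the result.** The article does not say this. Being randomised by mistake without the disease describes status at randomisation, and the diagnosis is checked beforehand. How such a case is adjudicated is detail an article may leave to the analysis plan.

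**Conclusion.** The point holds for safety and QTc. As written, the population rule drops dosed patients without cryptococcal meningitis from the adverse-event and QTc comparisons, and their final diagnosis is no reason to do so. The expected number is zero or very small. Each such patient who had an event would lower the arm's rate by about 3 to 4 percentage points over the counts tried (x = 1 to 6 of 25). Those counts, the assumed risks and the number of exclusions are illustrations, not figures from the protocol.

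No number in the protocol is wrong. The power statement is untouched, because the efficacy population would stay as it is. A reader might suspect that the rule conceals harm, but the recording and reporting routes make that too strong: what is lost is the patient's place in the final comparison. The wording of the primary-endpoint section is a minor matter of labelling.

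**What to change.** In *Analysis populations*, limit the exclusion of patients randomised by mistake without cryptococcal meningitis to the efficacy analyses. Add that the adverse-event and QTc analyses include every randomised patient who received at least one dose of study treatment, whatever the final diagnosis. Do not restrict this to a dose of the allocated regimen, because a patient given the other arm's pack would then be lost although exposed. Say also that in the control arm study treatment means the induction antifungals, so that the rule applies to both arms.

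In the primary-endpoint section, replace the loose label with a reference to the full analysis population as defined under *Analysis populations*.

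The cost is two or three sentences and no new data collection. The article reports that enrolment had finished and that analysis was still under way, so the change affects only which patients enter the safety tables.
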